### Randomization

Eligible and consenting participants will be randomized after completing baseline assessments to one of two groups: MBSR or LifeEd. A random permuted-block design (blocks of size 2 and 4) will be used, and the randomization with an allocation ration of 1:1 will be stratified by sex assigned at birth (male, female), cognitive status (cognitively normal, MCI), and MRI eligibility (eligible, not eligible) to ensure balance across these important factors. The biostatistician on the team, [name], prepared and maintains the randomization sequence for the eight strata. The project coordinator has been given concealed envelopes and only after a participant completes all pre-assessment sessions and is deemed eligible for the study does the project coordinator open the envelope from the respective stratum and assign the participant to either the MBSR or the LifeEd group. The project coordinator, the study facilitators and supervisors, and the study biostatistician will be the only members of the team who will be unblinded to group assignment. All personnel conducting assessments, behavioral or neuroimaging, will remain blind to group assignment.

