After preprocessing of behavioral and neuroimaging data, all data will first be tested for normality, outliers, and errors. We will then compute summary statistics and compare groups’ baseline demographic and clinical characteristics; although randomization should balance the groups with respect to these characteristics, with a finite sample size, there may be some residual imbalance. Particular attention will be paid to characteristics that may be associated with outcomes (e.g., education, depression scores) as chance imbalance in these characteristics may confound the intervention effects. All statistical analyses conducted as part of the trial will be intent-to-treat. The primary outcome variables for this study are indices of attentional control and mind-wandering. To examine the immediate effects of mindfulness training, we will use a linear mixed model to account for the within-subject correlation arising from measuring each subject at two timepoints. Group (MBSR, LifeEd), Time (pre and post-training), and the Group X Time interaction will be defined as fixed effects, with covariates, when applicable (e.g., those identified as randomly differing between groups) included as fixed effects. Each participant’s intercept will be included as a random effect. To determine the maintenance effects of mindfulness meditation, we will construct a separate mixed linear model examining the long-term efficacy of mindfulness meditation with Time (pre-training, 6-month follow-up, and 12-month follow-up), Group (MBSR, LifeEd), and the Group X Time interaction effects. Secondary factors of functional connectivity, fluid and everyday cognition, emotion dysregulation and inflammation will also be examined by constructing linear mixed models.

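### Covariates picked for chance imbalance and entered as main effects leave the Group X Time contrast essentially unadjusted; prespecify them, with the stratification factors, in a form that acts on change

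*Protocol article*

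**What the plan says.** The Data management and analysis section first compares the groups at baseline. It adds: "Particular attention will be paid to characteristics that may be associated with outcomes (e.g., education, depression scores", and gives the reason that "chance imbalance in these characteristics may confound the intervention effects".

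The model for the immediate effect is then set out: "Group (MBSR, LifeEd), Time (pre and post-training), and the Group X Time interaction will be defined as fixed effects". Further baseline variables may join this model, and the rule for them reads: "with covariates, when applicable (e.g., those identified as randomly differing between groups) included as fixed effects". On the random part: "Each participant’s intercept will be included as a random effect". Group X Time is the only interaction named.

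The maintenance model is described by "Time (pre-training, 6-month follow-up, and 12-month follow-up), Group (MBSR, LifeEd), and the Group X Time interaction effects", with no covariates named. Secondary outcomes are also to be analysed with linear mixed models.

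The Randomization section says that allocation "will be stratified by sex assigned at birth (male, female), cognitive status (cognitively normal, MCI), and MRI eligibility (eligible, not eligible"), which makes eight strata. The analysis text names none of these three factors in any model.

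**The concern.** Two things in the stated rule look wrong.

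- **The adjustment may not act on the quantity of interest.** The treatment effect is Group X Time, a difference between arms in change. A covariate that adds a constant to both visits of the same person does not touch that difference. If so, an adjusted primary result could be reported as having dealt with chance imbalance when it is essentially the unadjusted one.
- **The covariates are chosen by looking at the data.** The only inclusion rule given is an observed difference between arms. In a randomized trial such a difference is chance and says nothing about whether the variable predicts the outcome. The rule also tends to pass over sex, cognitive status and MRI eligibility, because stratified blocks keep those close to balance.

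At stake are the credibility of the adjusted primary analysis and, if the strata predict change, some precision.

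**Working it through.** The plan gives no figure for this adjustment, so there is none to reproduce. The check is algebra, followed by simulation with assumed values.

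**1. Inputs from the article.** Two visits; Group, Time and Group X Time as fixed effects; participant random intercept; covariates as fixed effects; 150 randomized 1:1; an expected 25% dropout (Sample size section).

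**2. Algebra with complete data.** Let x be a baseline covariate with coefficient γ:

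y(i,t) = β0 + β1·G + β2·t + β3·G·t + γ·x(i) + b(i) + e(i,t), with t = 0, 1.

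Subtracting the two visits gives

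y(i,1) − y(i,0) = β2 + β3·G + e(i,1) − e(i,0).

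Both γ·x(i) and b(i) are gone. The estimate of β3 is the difference in mean change, with or without x.

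If x also predicts change with slope δ, the change contains δ·x(i), and the unadjusted contrast shifts by δ × (imbalance in x). Only an x-by-Time term, or a model of the follow-up score, removes this.

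**3. Simulation.** Assumptions, none from the article: N = 150, residual intraclass correlation 0.6, imbalance 0.3 SD, δ = 0.3 per SD; 100 replicates of REML random-intercept fits.

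| Data | Change in Group X Time from main effects | SE ratio, main effects | Mean change from Covariate X Time |
|---|---|---|---|
| Complete | 0 (largest 3e-15) | 1.000 | −0.089 |
| About 25% covariate-related dropout | mean absolute 0.023, largest 0.080 | 0.991 | −0.074 |

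- One complete data set gave 0.30588 (SE 0.1425) both without the covariate and with it as a main effect.
- The −0.089 agrees with δ × imbalance = 0.3 × 0.3 = 0.09.
- With dropout, 0.023 against a typical SE of 0.178 is 0.023/0.178 = 0.13 SE. The mean signed shift was only 0.007, so this is a by-product of missingness rather than a correction of the imbalance.
- A complete three-visit data set behaved in the same way: 0.058256 and 0.092729 in both fits.

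For scale, with 75 per arm a mean difference in x has standard error √(2/75) = 0.163 SD. An imbalance of 0.3 SD is thus 0.3/0.163 = 1.84 standard errors: uncommon for any one covariate, but possible.

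**4. Stratification factors.** Suppose the strata explain a share R² of the variance in *change* and are balanced by design. The unadjusted SE is then too large by 1/√(1 − R²), and a nominal two-sided 5% test has true size 2·[1 − Φ(1.96/√(1 − R²))].

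- R² = 0.10: inflation 1.054; size 2·[1 − Φ(2.066)] ≈ 3.9%.
- R² = 0.20: inflation 1.118; size 2·[1 − Φ(2.191)] ≈ 2.8%.

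Simulation put these sizes at about 3.6% and 2.7%, which is the same picture. If the strata affect *level* only, they cancel as in step 2, and simulated size stayed at about 5%.

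**The case against.** The strongest reply is that nothing here harms the primary test. Under randomization the unadjusted Group X Time contrast is valid, and the planned main effects leave it almost intact. Group X Time already removes imbalance in anything that affects level only. If the selected covariates cancel, choosing them after seeing the data can hardly move the result. All of that stands, and it sets the weight of the point.

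The article is also a condensed text. Its covariate list is open, and entering covariates as fixed effects does not strictly exclude a covariate-by-Time term. A full analysis plan may name the stratification factors. That answers any complaint about omission, but not the rule that is stated: the one selection criterion given is chance difference, and the one interaction named is Group X Time.

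Four stronger readings are tempting, and the text does not support them:

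- *The covariates can never change the estimate.* This is exact only with complete data.
- *The selection ignores prognosis.* The same section directs attention to characteristics linked to outcome and names education and depression scores. The defect is that the inclusion rule does not use that criterion.
- *The stratification factors are excluded.* They are not named, which is weaker.
- *Leaving out the strata inflates the SE of this model by 5–12%.* That holds only if they explain 10–20% of the variance in change. The article gives no such figure, and the same share of variance in level costs the change contrast nothing.

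**Conclusion.** The point holds in a limited form. On the natural main-effect reading, the stated adjustment does not do the job that the section gives it. With complete data it leaves Group X Time and its SE unchanged. With dropout near the expected 25% it moves the estimate by about 0.13 SE on average in one illustrative setting. Confounding by a covariate that predicts change would remain: 0.09 if the imbalance were 0.3 SD and the slope on change 0.3, both assumed.

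The selection rule is data-dependent and unlikely to reach the factors the trial randomizes by. As written, this has little effect on the primary contrast, because the selected covariates cancel. It would matter once covariates enter in a form that works, so the rule and the form of entry should be changed together.

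No bias on average and no inflated type I error is shown. The possible cost of omitting the strata is a conservative test, and only if they predict change. This is a cheap improvement to the analysis, not a must-fix.

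**What to change.** 1. Delete the chance-difference criterion. Keep the baseline comparison as description only.
2. Name the covariates in advance for the immediate, maintenance and secondary models: sex, cognitive status and MRI eligibility, plus the prognostic variables the section already mentions, such as education and depression score.
3. Enter them in a form that acts on the contrast: either each covariate with its Time interaction in the mixed model, or as covariates in a model of the follow-up score adjusted for baseline. Adding the stratification factors as main effects alone would not help, because they would cancel too.

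The baseline-adjusted option may also gain precision. Per unit of outcome variance, its variance is 1 − ρ² against 2(1 − ρ) for change: 0.91 against 1.40 at ρ = 0.3, 0.75 against 1.00 at 0.5, and 0.51 against 0.60 at 0.7 (ρ is assumed; the article gives none).

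The cost is a change of wording and a few degrees of freedom. The stratification factors are known at randomization, the depression scale is part of screening, and education is already needed for the normed scores. The change should be fixed before outcomes are compared by arm.

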### Sample size

In our pilot study [34], we found a partial eta square of 0.088 for the repeated-measures ANOVA examining the effect of mindfulness on Go/No-Go performance as a function of working memory index. Based on an alpha of 0.05, a total sample size of 103 would be needed to yield an estimated power greater than 0.80. Given the attrition observed in our pilot study (~ 20%), the 12-month duration of the proposed intervention, and multiple assessment sessions, we will recruit at least 130 participants to account for a potential 25% drop-out rate. Power analysis for the imaging data was based on the parameter estimates in the Kilpatrick study [52] examining the impact of mindfulness training on functional connectivity of resting-state networks. The resulting effect sizes were *d* = 1.29 and *d* = 0.99 for auditory/salience regions To be conservative, we used the effect size of *d* = 0.99. To detect an effect of this size with 90% power, we would need 23 subjects per group for a total of 46 people. A study by Kilpatrick and colleagues [52] compared their mindfulness intervention against a wait-list control group. It is likely that the parameter estimates of their study include variance that may be accounted for by non-specific factors. In the present study, our mindfulness training group will be compared with an active control group that will control for many of the non-specific factors. Thus, assuming an effect size of *d* = 0.76, we plan on collecting MRI data on 75 participants to yield an estimated power greater than 0.90.

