### Study interventions

#### Mindfulness-Based Stress Reduction (MBSR) program

The MBSR program being offered in this study is modeled after the eight-week program developed and popularized by Jon Kabat-Zinn to reduce pain and stress [24]. The MBSR program is offered in a group setting wherein participants meet with trained facilitators once a week for two and a half hours each (except for the first class which is three hours) along with a four-hour retreat offered on a weekend (between weeks six and seven)—thus resulting in 24.5 h of face-to-face training. In these classes, facilitators cover a combination of experiential practices, didactics and teachings on the topics of mindfulness, and mindful movement exercises. These practices and teachings all center on cultivating present moment awareness in a framework that promotes acceptance and non-judgment. Moreover, the participants are provided with several opportunities to engage in small and large group-based discussions that offer a platform for social support, validation, and shared experiences. Supplementary Table 1 provides the agenda for each of the eight sessions of the MBSR program as well as the practices taught during the retreat. In addition to these classes, all participants are invited to engage in 30 min of formal homework practices, delivered through our web/mobile-based, in-house application that was named after the study—HealthyAgers. Working with a team of inter-disciplinary experts, including certified mindfulness experts, psychologists, wellness coaches, and computer programmers, we have carefully designed this iOS/Android mobile/web application to deliver and track guided meditation practices. This application will allow us to collect objective practice data on all our participants with the application providing information on minutes practiced, the frequency of engagement in mindfulness practices per week, and additional meta-data, including preferred practices, time of day preference, etc. After the eight weeks of the intervention, participants will be invited to continue engagement with mindfulness practices on their own, five times per week, for 12 months with two-hour, group-based booster sessions provided by the study facilitators every three months. Prior to the pandemic, all intervention sessions were provided in our group psychotherapy rooms housed in the Department of Psychology. Sessions shifted to the Zoom platform in March 2020 and continue to be offered virtually.

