#### Lifestyle Education (LifeEd) program

The LifeEd program is an active control group against which we will compare the effects of the MBSR program. Participants are provided with psychoeducation on topics related to healthy living and wellness for older adults. The series includes didactics covering the latest evidence-based science on: sedentary behavior, physical activity, cognitively stimulating activities, social support, sleep, stress management, nutrition, and hydration. This program is designed to control the many active ingredients of a group-based psychotherapeutic program, like MBSR. As such, it is matched for setting (group), number and training of facilitators, amount of time receiving in-person instruction, and amount of assigned homework time. In addition, to ensure that it is matched with respect to engagement in experiential exercises, participants are introduced to light stretching and toning exercises during the two-and-a-half-hour class sessions. These stretching and toning exercises were designed by a certified yoga instructor with expertise in working with older adults. Supplementary Table 1 also provides detailed agendas for all eight sessions of the LifeEd program. Moreover, participants in the LifeEd program also have access to the web/mobile application—HealthyAgers—with participants in this group engaging in the following combination of homework practices: light stretching and toning exercises three times/week, reading two popular press articles and answering questions related to them once a week, and watching one to two videos and answering related questions once a week. All homework materials are standardized to take ~ 30 min with all readings and videos delivered through the in-house application. Finally, like the MBSR program, participants in the LifeEd group are also being provided booster sessions once every three months with the encouragement to continue completing homework practices five times per week. Prior to the pandemic this group also met in-person with trained facilitators and transitioned to Zoom sessions starting in March 2020 because of the COVID-19 pandemic.

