The three most common control groups included across the studies on mindfulness meditation involved relaxation controls, education groups, and book reading groups. Importantly, factors of social support, such as collaborative discussion within group formats and engagement in cognitively stimulating activities, were highlighted as key non-specific factors influencing attention. Our control group—the Lifestyle Education Control Group—has been matched with respect to multiple metrics. Format of delivery: both protocols were delivered in-person before the COVID-19 pandemic, and we shifted to a virtual format (after the pandemic), offering classes synchronously via the Zoom platform with participants recruited in groups of six to eight for peer support. Timing: each of the eight weekly classes (plus the retreats) is matched for timing. Content: both protocols have a mix of didactics, experiential practices, social support, and community building. Peer support: qualitative analysis of focus group discussions on mindfulness-based interventions[103–105] highlight the need for participants to connect and communicate with others engaging in the interventions. Both groups have built-in dyadic and small-group discussions on topics such as weekly materials, challenges with homework practices, and overall learning in the program. Homework assignment: both programs require engagement in daily homework assignments through our in-house application for 30 min/day for five days/week.

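### Both arms are taught in small classes, but the primary mixed model has no class term; if classes differ in mean change, the Group X Time standard error is too small

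*Protocol article*

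**What the plan says.** Under Randomization, individuals are allocated 1:1. Treatment is then given in classes. For the mindfulness arm: "The MBSR program is offered in a group setting wherein participants meet with trained facilitators once a week". The control program is clustered too: "it is matched for setting (group), number and training of facilitators". The Discussion gives the class size: "participants recruited in groups of six to eight for peer support". It also says that both programs build in paired and small-group discussion.

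Under Data management and analysis, the primary model is set out as follows: "we will use a linear mixed model to account for the within-subject correlation arising from measuring each subject at two timepoints". The fixed effects are Group, Time, their interaction and any covariates. For the random part, each participant's "intercept will be included as a random effect". No class or facilitator term is named, for this model or for the separate maintenance model at 6 and 12 months.

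Under Sample size, the calculation starts from the pilot: "we found a partial eta square of 0.088 for the repeated-measures ANOVA". It arrives at 103 participants for power above 0.80 at alpha 0.05 and then allows only for 25% dropout.

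**The concern.** Members of one class share facilitators, discussion and peers for eight weeks. If this makes their changes more alike than those of people in other classes of the same arm, they are not independent observations of the treatment effect.

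The participant intercept cannot absorb this. It describes what is constant in a person across visits, whereas a class can act only after baseline. Fixed covariates chosen for baseline imbalance do not help either, because classes are nested within arm.

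At stake are the width of the confidence interval for Group X Time, the true level of the nominal 5% test, and the power that the trial can claim. The article states the random-effects structure and names the one correlation it is meant to handle. This is therefore a stated model, not a detail left to a statistical analysis plan.

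**Working it through.** **Inputs from the article.** Class size at recruitment: 6 to 8 (Discussion), midpoint 7. Dropout: 25% (Sample size). Effect: partial eta squared 0.088. Alpha: 0.05. Required N: 103. Planned total: 150 (Study design).

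**Assumed.** The ICC of change scores within class, taken as 0.01, 0.02, 0.05 and 0.10, because the article gives none.

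**Step 1: reproduce the stated N.** f² = 0.088 / (1 − 0.088) = 0.0965. With λ = f² × N in a noncentral F test:
- 2 numerator df: N = 103 gives power 0.800, an exact match.
- 1 numerator df: N = 84 is enough for 0.80, and N = 103 gives 0.877.

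The 103 therefore treats participants as independent and contains no hidden design effect. It also corresponds to a 2-df test, whereas the planned two-group, two-time interaction has 1 df. Both are carried forward.

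**Step 2: what the model tests.** With complete pre and post data and only a participant intercept, the Group X Time test equals a t-test on change scores. Write change = arm effect + class effect + individual residual. The ICC is the class share of the variance of change within arm.

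**Step 3: true error.** Design effect DE = 1 + (m − 1) × ICC. The true standard error is √DE times the model's. Actual two-sided error = 2 × [1 − Φ(1.96 / √DE)].

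For m: 7 × 0.75 = 5.25 analysed per class after dropout; 7 with no dropout. Example at m = 5.25 and ICC 0.05: DE = 1 + 4.25 × 0.05 = 1.2125; √DE = 1.101; 1.96 / 1.101 = 1.780; error = 7.5%.

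| ICC | DE, m = 5.25 | SE ratio | Error | DE, m = 7 | SE ratio | Error |
|---|---|---|---|---|---|---|
| 0.01 | 1.043 | 1.02 | 5.5% | 1.06 | 1.03 | 5.7% |
| 0.02 | 1.085 | 1.04 | 6.0% | 1.12 | 1.06 | 6.4% |
| 0.05 | 1.213 | 1.10 | 7.5% | 1.30 | 1.14 | 8.6% |
| 0.10 | 1.425 | 1.19 | 10.1% | 1.60 | 1.26 | 12.1% |

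A simulation (40,000 trials per setting, 150 participants, 7 per class) gave 5.5% / 6.3% / 8.6% / 12.1% for the test without class. A class-level test on the same data gave 4.8% to 5.0%.

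**Step 4: power of a valid test.** λ becomes f² × N / DE, with N = 103 and m = 5.25.

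| ICC | 2-df calculation (reproduces N) | 1-df Group X Time (planned) |
|---|---|---|
| 0 | 0.80 | 0.88 |
| 0.02 | 0.77 | 0.85 |
| 0.05 | 0.72 | 0.81 |
| 0.10 | 0.64 | 0.74 |

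If 150 are enrolled and 25% are lost (about 112 analysed), the 1-df figures are 0.88 / 0.84 / 0.78 at ICC 0.02 / 0.05 / 0.10. All of these keep individual-level residual df. A test on class-level df would have slightly less power.

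**The case against.** **The ICC may be near zero.** Sessions follow manuals with agendas and transcripts, facilitators are trained alike, and new ones are supervised weekly. Missed sessions are made up individually or by a summary. Much of the practice is app-based homework: 30 minutes × 5 days × 8 weeks = 20 hours, against 24.5 hours of class time in the mindfulness arm. The outcomes are computer-task measures taken by blinded assessors. All of this stands as a reason not to presume a large ICC, but none of it shows that the ICC is zero.

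**The article's own remark on group factors is weak evidence.** The Discussion says that social support and group discussion "were highlighted as key non-specific factors influencing attention". That summarises literature on control groups, and a factor that shifts every class equally creates no variance between classes. This is correct: the remark makes a positive ICC plausible and does not quantify it. Equally, matching the arms on group format protects the mean contrast from bias but does not remove variation between classes within an arm.

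**The decision rule.** The article will claim efficacy for attention only with improvement on both tasks, and for mind-wandering only with reductions in both probes and response-time variability. When both effects in a pair are null, the joint false-positive rate is below the per-test rate, unless the two tests always agree. If they were independent, 10.1% would become 0.101 × 0.101 = 1.0%. The per-test rate carries over to the claim only where the other measure's effect is real. This stands and limits the conclusion.

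**Class size.** Six to eight appears in a sentence about the virtual format, and no separate size is given for classes before the pandemic. Those were group classes too, so the structure is the same, but m for them is an assumption.

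**Conclusion.** The omission is real and should be fixed, but its consequence is conditional. If the class ICC of change is above zero, the planned standard error for Group X Time is too small. Per-test error is then about 5.5% to 10.1% over ICC 0.01 to 0.10 after the planned dropout, or 5.7% to 12.1% with full classes of seven. The effect is modest at 0.01 to 0.02 and material from 0.05.

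A reader might infer three stronger statements, and the article supports none of them:
- *The primary test certainly exceeds 5%.* No ICC is given, and at ICC 0 the test holds its level.
- *Efficacy will be falsely declared at these rates.* They are per-test rates, counting both directions, and the both-measures rule lowers the joint rate when both effects are null.
- *The trial is underpowered.* For the 1-df test that is planned, power with 103 analysed stays at about 0.81 at ICC 0.05 and falls below 0.80 only towards 0.10.

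Confidence is high that the term is missing and in the direction of its effect, and moderate in the size. Severity: should fix.

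**What to change.** 1. In the primary model, add a random effect for intervention class, nested in arm, that acts on post-baseline visits. Use a class-by-time effect in the mixed model, or a class intercept in an ANCOVA of the post-training score. A class intercept that is constant over time is not enough, because it cancels out of Group X Time.
2. Do the same in the maintenance model.
3. Use Satterthwaite or Kenward-Roger degrees of freedom.
4. Restate power for the 1-df Group X Time test over a stated ICC range, with the class size expected after dropout. Enrolment need not change.

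**Cost.** One extra variance component and some wording. Class membership should already be on record, since attendance is recorded for each participant, so no new outcome data are needed. With 150 / 8 to 150 / 6, or about 19 to 25 classes, inference would rest on about 20 cluster-level degrees of freedom (classes minus two arms: 17 to 23). Intervals would be slightly wider even if the ICC turned out to be near zero. The article describes recruitment as ongoing, so its wording leaves room to make the change before results are known.
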